## Figures and Tables

**Figure 1 fig1:**
[figure not shown]
Flowchart of stage 1 of the trial.

**Figure 2 fig2:**
[figure not shown]
Selection and location of the acupoints for acupuncture.

**Figure 3 fig3:**
[figure not shown]
Main structure of the sham acupuncture needle.

**Figure 4 fig4:**
[figure not shown]
Acupuncture needle base.

**Figure 5 fig5:**
[figure not shown]
Real needle and sham needle.

**Figure 6 fig6:**
[figure not shown]
Flowchart of stage 2 of the trial.

**Figure 7 fig7:**
[figure not shown]
The relationship between PD and PDA.

**Table 1 tab1:** The timeline of participant progress through stage 1.

	Baseline visit	Intervention (weeks 1–4)				Follow-up period
Time point	Week 0	Week 1	Week 2	Week 3	Week 4	Week 12
Signing consent	●					
General examination	●					
Inclusion/exclusion	●					
Grouping	●					
Medication status	●					●
Acupuncture/sham acupuncture	●	●	●	●	●	
HAMA	●				●	●
UPDRS	●				●	●
Hoehn–Yahr Rating Scale	●				●	●
SF-36 scale	●				●	●
Serological indicators	●				●	
Adverse events		●	●	●	●	
Safety assessment		●	●	●	●	

HAMA: Hamilton Rating Scale for Anxiety; UPDRS: Unified Parkinson's Disease Rating Scale.

**Table 2 tab2:** Timeline of the progress of the participant in stage 2.

	Baseline visit	Intervention (weeks 1–4)			
Time point	Week 0	Week 1	Week 2	Week 3	Week 4
Signing consent	●				
General examination	●				
Risk factor	●				
Medication status	●				
Safety eligibility	●				
Allocation	●				
Acupuncture + anti-Parkinson drugs + CMO		●	●	●	●
Anti-Parkinson drugs + CMO		●	●	●	●
Feasibility and universality					●
Cost effectiveness					●
HAMA	●				●
UPDRS	●				●
Hoehn–Yahr Rating Scale	●				●
SF-36 scale	●				●
Serological indicators	●				●
Adverse events		●	●	●	●
Safety assessment		●	●	●	●

CMO: clinical monitoring only; HAMA: Hamilton Rating Scale for Anxiety; UPDRS: Unified Parkinson's Disease Rating Scale.

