## Abstract

Parkinson's disease anxiety (PDA) is a nonmotor symptom of Parkinson's disease (PD) that is often neglected. PDA poses a far-reaching challenge to the treatment of PD. Acupuncture could be successful in the treatment of PDA. However, the evidence for this is still limited. We propose a two-stage clinical trial. In stage 1, a total of 70 volunteers with PDA will be randomly assigned to either acupuncture (manual acupuncture) or control group (sham acupuncture) in a 1 : 1 ratio. Treatments will be performed for four weeks. The change in the Hamilton Rating Scale for Anxiety (HAMA) score from baseline to week 4 and week 12 will be the primary outcome. The levels of adrenocorticotropic hormone (ACTH), cortisol (CORT), serotonin (5-HT), and corticotropin-releasing factor (CRH) in the patients' serum and the scores on the Hoehn–Yahr Rating Scale and the Unified Parkinson's Disease Rating Scale (UPDRS) will all be considered among the secondary outcomes. Participants will be followed up until week 12. In stage 2, a total of 82 volunteers with PDA will be randomly assigned to either an acupuncture (manual acupuncture) or a control group (anti-Parkinson drugs only) in a 1 : 1 ratio. HAMA score will be the primary outcome. Universality, feasibility and cost effectiveness, Hoehn–Yahr Rating Scale, UPDRS, and serological indicators will be secondary outcomes. Participants will be followed up until week 4. The statistical analysis will include all the allocated individuals. The First Affiliated Hospital of Guangzhou University of Traditional Chinese Medicine's Research Ethical Committee authorized this procedure, and the trial is registered with ChiCTR2100047253.

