### 3.4. Primary Outcome

The change in the HAMA score from baseline will be the primary outcome, measured at baseline and week 4. We will also use this scale during the follow-up period at week 12 to assess the anxiety status of the patients after they leave the group. HAMA is one of the first rating scales used to measure the severity of perceived anxiety symptoms and is often used in clinical trials. It consists of 14 symptomatic definition elements that reflect psychological and physical symptoms. Each item is rated on a scale of 0 to 4, for a total possible score of 56. Mild anxiety is indicated by a score of 17–24, whereas severe anxiety is indicated by a score of 25–30.

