#### 3.5.2. UPDRS and the Hoehn–Yahr Rating Scale

In addition to the assessment of patient anxiety, PD-associated nonmotor and motor symptoms are also a focus of our study. Hoehn–Yahr Rating Scale and UPDRS will therefore be employed in this study. The clinical assessment of PD mainly relies on the UPDRS. This scale, which provides cardinal evidence for determining the clinical classification, has been applied for 20 years as a comprehensive assessment tool to monitor disease progression and evaluate the therapeutic efficacy of PD treatments. The instrument assesses four aspects: (1) mood, mental status, and behavior; (2) daily life activities; (3) motor evaluation; and (4) problems of therapy. Based on the total score, PD can be divided into five grades: normal, mild, moderate, severe, and extremely severe. The Hoehn–Yahr Rating Scale, another scale applied in this trial, has been used for the staging of functional disability linked with PD. It describes the progression of PD-related symptoms through various stages, thus allowing us to assess the intensity of the disease. The above two scales will be completed under the guidance of professional personnel at baseline and weeks 4 and 12.

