### 4.2. Safety Evaluation

During the acupuncture of the participants, acupuncture operators will truthfully record adverse reactions, such as dizziness, broken needles, hematoma, and infection. At the same time, the operators will record and evaluate the treatment for adverse reactions. If patients drop out of the trial owing to adverse reactions, the reason for dropout and the last treatment time will be recorded, and the assessment items that can be completed before the end of the trial will be completed. After the end of the trial, the patient data will be collected and appropriately stored. Dropouts owing to adverse reactions will be included in a statistical analysis of adverse reactions.

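### Stage 1 schedules adverse-event collection for weeks 1 to 4 only, leaving the existing week 12 visit unused for reactions that appear after treatment ends

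*Protocol article*

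**What the plan says.** Table 1 sets out stage 1 visit by visit: week 0, weeks 1 to 4 of intervention, and a follow-up column at week 12. The rows "Adverse events" and "Safety assessment" are marked at each of weeks 1 to 4. Both are empty at week 12. In that same column HAMA, UPDRS, Hoehn–Yahr, SF-36 and medication status are marked.

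Section 4.2 describes who records safety data and when: "During the acupuncture of the participants, acupuncture operators will truthfully record adverse reactions, such as dizziness, broken needles, hematoma, and infection". Its only other provision for capturing events concerns withdrawals: "If patients drop out of the trial owing to adverse reactions, the reason for dropout and the last treatment time will be recorded". It names no collection point after treatment.

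The Abstract says of stage 1 that "Participants will be followed up until week 12". Section 3.4 says of HAMA, "We will also use this scale during the follow-up period at week 12", and Section 3.5.2 says of UPDRS and Hoehn–Yahr, "The above two scales will be completed under the guidance of professional personnel at baseline and weeks 4 and 12". Section 4.1 gives SF-36 the same time points.

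**The concern.** The adverse-event schedule stops with treatment, while efficacy and quality of life are followed for a further 8 weeks. Some reactions named in Section 4.2 are evident at once, such as dizziness or a broken needle. Infection can take time to show. A reaction to an early session can be picked up at the next one. A reaction to the last sessions has no next session, and the people assigned to record reactions are the operators, whose treatment role ends at week 4.

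What is at stake is the completeness of the stage 1 safety summary. As scheduled, it can describe reactions seen while treatment was running. It cannot support a statement that no delayed reactions occurred, because nobody is scheduled to ask. A second, smaller point is that the operators know which needle they use (Section 2.7), whereas Section 7 says the evaluators are blinded. A question at week 12 could come from someone who does not know the arm.

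**Working it through.** The plan gives no figure to reproduce. The check sets the relevant places side by side.

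**Inputs**

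| Item | Source | Content |
|---|---|---|
| Treatment length | Abstract; Sections 3.1 and 3.2 | 4 weeks |
| Stage 1 follow-up | Abstract; Table 1 | to week 12 |
| Adverse-event row | Table 1 | weeks 1, 2, 3, 4; week 12 empty |
| Safety-assessment row | Table 1 | weeks 1, 2, 3, 4; week 12 empty |
| Who records, and when | Section 4.2 | operators, during acupuncture |
| Week 12 assessments | Table 1; Sections 3.4, 3.5.2, 4.1 | HAMA, UPDRS, Hoehn–Yahr, SF-36; medication status (Table 1 only) |

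**Step 1: are the empty cells real?** Five other rows keep their week 12 mark, so the column was not lost in conversion. It is not wholly reliable, though: the serology row is also empty at week 12, while Section 3.5.1 says the serum markers are measured then. For serology the text contradicts the empty cell. For adverse events the text agrees with it, because Section 4.2 ties recording to acupuncture. The schedule therefore rests on two places that agree, not on a blank cell alone.

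**Step 2: length of the gap.** Weeks without scheduled collection = follow-up − treatment period = 12 − 4 = 8 weeks, and 8 / 12 = 67% of stage 1 follow-up. This is calendar time after needling has ended. It is not 67% of exposure, nor 67% of expected events.

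**Step 3: which events can be missed?**

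- Reaction to a session in the first weeks: sessions recur within days, so it can be noted at a later session.
- Reaction to a final session, noticed by the week 4 assessment: Table 1 marks both safety rows at week 4, so it can be recorded.
- Reaction to a final session, first appearing or noticed after the week 4 assessment: no scheduled collection.
- Reaction that leads to dropout: Section 4.2 provides for it, but gives no collection point after treatment.

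Only the third group clearly falls outside the schedule. Infection fits it best. A hematoma would usually be visible soon after needling and is a weak example.

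**The case against.** The strongest reply is that nothing here is wrong. Table 1 and Section 4.2 agree, and the listed reactions are procedural, so a window matching the treatment period is defensible. Section 3.4 presents week 12 as a check on anxiety after patients have left the group. The article also condenses a fuller protocol that may contain a reporting rule. Much of this stands: there is no contradiction on this point, and the choice is not unreasonable. But the article does not leave the timing open. It prints explicit safety rows that end at week 4, and its text agrees, so the schedule can be judged as stated.

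Three stronger readings are tempting and should not be drawn.

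- A reader might infer that every event after the last session is lost. The documents do not say so. Week 4 is marked, and spontaneous reports are not excluded. What is missing is scheduled collection after week 4.
- A reader might measure the loss by the confidence bound for zero events among 35 acupuncture patients, 1 − 0.05^(1/35) = 8.2% (one-sided 95%). That figure depends only on arm size. It would be the same with week 12 marked and says nothing about how many late events exist.
- A reader might infer that the stage 2 hypothesis of fewer side effects (Section 7) depends on this gap. It does not. Stage 2 assesses side effects itself over weeks 1 to 4 (Section 5.2.3, Table 2), its follow-up ends at week 4, and Section 5 makes entry to stage 2 depend on efficacy.

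**Conclusion.** The point holds as a minor, inexpensive improvement. Stage 1 schedules no adverse-event or safety collection after week 4, although the same patients are assessed at week 12. The safety summary therefore covers the treatment period only and should be described that way if the schedule stays as it is.

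The gap is 8 weeks of calendar time. Its effect on event counts cannot be computed, since the article gives no event rate, and it is confined to delayed reactions to the final sessions.

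The conclusion rests on two assumptions: that the empty week 12 cells mean what they show, which Section 4.2 supports, and that no fuller document adds post-treatment collection. If one does, Table 1 and Section 4.2 need only be brought into line with it.

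**What to change.** 1. In Table 1, mark the adverse-event and safety-assessment rows at week 12.
2. In Section 4.2, extend recording beyond the needling sessions to the week 12 visit.
3. At week 12, have the blinded evaluator ask one standard question, worded identically in both arms, about any adverse event since the week 4 assessment, and record the onset date.
4. Report events with onset up to week 4 separately from those with later onset.

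The cost is one question and a few fields on the case report form at a visit that already takes place. No new visit, treatment change or sample-size change is needed. The drawback is that some events unrelated to needling will be recalled over 8 weeks. Onset dates help separate those soon after the last session from later ones, and asking both arms alike allows a comparison with sham. Table 2 needs no matching change, because stage 2 follow-up ends at week 4.

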## Data Availability

No data were used to support this study.
